### Participant Recruitment and Eligibility

The BRAVE intervention is designed for mobile phones with internet capabilities and is targeted toward young adult veterans. Though the intervention is designed for use on mobile phones, it can be accessed through computers and tablets. Given the focus on a younger veteran cohort, eligibility criteria include (1) US veteran who has been discharged or separated from the Air Force, Army, Navy, Marine Corps, or Coast Guard (participants could have also been in the reserves or guard units, but not on active duty), (2) between the ages of 18 and 40 years, (3) a score on the 10-item Alcohol Use Disorders Identification Test (AUDIT [54]) of 4 or greater (men) or 3 or greater (women), which represents cutoff scores to identify those who may benefit from interventions to reduce alcohol misuse, (4) no upcoming appointments at the VA or elsewhere to receive treatment for a behavioral health concern (such as depression, PTSD, or alcohol use concerns), and (5) no appointments in the past six months for behavioral health treatment at a VA or elsewhere. The purpose of these latter 2 criteria is to reach participants outside of traditional care settings (ie, those who may need care but who are not receiving it) and to measure the effect of the intervention on treatment initiation. Participants also need access to the internet via a computer, tablet, or phone; a working email address; and the ability to read and understand English. Based on these criteria, we will recruit 800 participants who will be randomly assigned to the BRAVE intervention (n=400) or a resources-only control condition (n=400) that presents resources for care seeking (eg, location of local VA and links for connecting with local veteran service organizations) without any personalized content.

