#### Primary Outcomes

Primary outcomes are drinking behavior (past 30-day frequency, quantity, and number of binge-drinking days), negative alcohol-related consequences, and treatment initiation. Three past 30-day drinking outcomes will be assessed through single-item self-reports: drinking days, average drinks per occasion, and binge drinking days. Alcohol-related consequences in the past 30 days will be assessed with the Short Inventory of Problems [68], which is modified from the Drinker Inventory of Consequences [69]. The treatment outcome will be measured as treatment initiation in the time period after the intervention (ie, post baseline). Treatment initiation is assessed with an item asking participants to indicate if they have seen a provider at a VA or non-VA care setting for therapy, counseling, support groups, hospitalization, or medications for any concerns related to alcohol or substance use (eg, if they sought help to drink less, or attended groups to stay abstinent from cannabis or other drugs) or mental health concerns (eg, to help with stress, anxiety, depression, nightmares) in the past 6 months (at baseline) and past 3 months (follow-ups). Providers are defined for participants as a mental health or behavioral health provider (eg, psychiatrist, psychologist, social worker, mental or behavioral health nurse, or other providers), a general medical provider (eg, primary care doctor, physician assistant, and nurse practitioner), or an addiction specialist (eg, addiction counselor). Care is specified as either in-person or via telehealth.

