### Analytic Plan

#### Overview

Prior to the main aims analyses, we will assess for multivariate normality. The maximum likelihood estimator will be used if data are approximately normal and robust maximum likelihood will be used if the data are not multivariate normal. Missing data will be assumed to be missing at random and handled using direct maximum likelihood techniques. We will assess for differences in baseline demographics and military characteristics between the intervention (BRAVE) and control conditions. Any characteristic significantly different between groups will be controlled for in analyses.

To assess the effects of the intervention on continuous primary outcomes (drinking days, average drinks per occasion, binge drinking days, negative alcohol-related consequences, and treatment initiation) and secondary outcomes (preparatory behaviors, readiness to seek care ruler for alcohol, readiness to seek care ruler for mental health), a taxonomy of latent growth models will be estimated [75]. The primary outcome time point for this trial will be the baseline to first follow-up (ie, 3 months post baseline); however, we are interested in the past 30-day changes from baseline to each of the 3 additional follow-up timepoints (ie, baseline to 6, 9, and 12 months post baseline). To assess between-group differences in the intercept and growth factors, we will regress each on a dummy variable representing the intervention (BRAVE=1) and control (control=0) groups. For any count variables, negative binomial or Poisson distributions will be explored for better model fit. To understand the change in treatment initiation (binary outcome), we will use latent growth models with categorical outcomes, as well as estimate simple logistic regression at each time point. To understand the practical significance, we will calculate standardized mean differences (Cohen *d*) at all 4 follow-up time points for both between group and within group.

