#### Power Analysis

Given this study design (and standard *P*<.05; 2-tailed testing), we will have 80% power to detect small treatment effects between the groups; specifically, effects of d=0.22 at 3- and 6-month follow-ups and d=0.23 at 9- and 12-month follow-ups. For reference, our observed intervention effect sizes at 1 month post intervention in the pilot study were *d*=0.17 for average drinks, *d*=0.18 for binge days per month, and *d*=0.19 for consequences [49]. We have similarly found small effect sizes over 2 years of follow-up in other large-scale PNF studies [76-78]. We expect effect sizes to be small, though slightly larger than those in our prior work given we include a sample screening positive for hazardous alcohol use that could benefit from treatment, whereas prior work targeted general college students and young veterans drinking at less severe levels. As noted, given that this intervention targets those who may never have received care otherwise, small effects seen in brief interventions, such as this, are potentially clinically significant.

Our prior work evaluating treatment-seeking behaviors has found rates of preparatory and actual treatment-seeking by service members to increase by double following brief phone-based feedback [79]. Other work has similarly found rates of substance use treatment initiation to increase to upwards of 50% following in-person feedback–based approaches [80]; thus, we hypothesize that upwards of 50% of participants who receive the enhanced PNF will report actual treatment initiation at some point during the 12-month follow-up period. We will examine preparatory behaviors (ie, steps along the way to actual initiation) and motivation to seek care.

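### The growth model for treatment initiation appears to start from a baseline that eligibility sets at or near zero, so neither its intercept nor its slope alone measures the intervention effect, and the plan does not say whether it or the logistic regression decides

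*Protocol article*

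**What the plan says.** The Primary Outcomes section makes treatment initiation a primary outcome: "Primary outcomes are drinking behavior (past 30-day frequency, quantity, and number of binge-drinking days), negative alcohol-related consequences, and treatment initiation". It places the outcome after the intervention: "The treatment outcome will be measured as treatment initiation in the time period after the intervention (ie, post baseline". The item asks about care received "in the past 6 months (at baseline) and past 3 months (follow-ups").

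Participant Recruitment and Eligibility requires "no appointments in the past six months for behavioral health treatment at a VA or elsewhere".

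The Overview of the Analytic Plan first puts treatment initiation among the "continuous primary outcomes (drinking days, average drinks per occasion, binge drinking days, negative alcohol-related consequences, and treatment initiation"). These outcomes go into latent growth models in which the intercept and growth factors are each regressed on arm, and the primary time point is baseline to 3 months. The same paragraph then calls the outcome binary: "To understand the change in treatment initiation (binary outcome), we will use latent growth models with categorical outcomes". The sentence goes on to a second analysis, so that its full plan is "we will use latent growth models with categorical outcomes, as well as estimate simple logistic regression at each time point". It does not rank these two analyses, and it gives no separate time origin for treatment initiation.

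The only rate stated for this outcome is in the Power Analysis section: upwards of 50% of those receiving the intervention "will report actual treatment initiation at some point during the 12-month follow-up period". No control rate and no rate per visit is given.

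**The concern.** A growth model of change from baseline needs a baseline that carries information. Here the entry criterion and the baseline item look back over the same six months, so both arms start at or close to zero by design. A straight line on the logit scale cannot follow a jump from zero to a plateau. It settles on a fitted baseline well above zero, and if the arms differ at follow-up, it places much of that difference in the fitted baseline.

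The two parameters that the plan regresses on arm then lose their usual meaning. The intercept effect describes a time at which the arms cannot differ, and the slope effect can be close to nil when BRAVE helps equally at every visit. The logistic regression planned beside it could show a clear benefit at 3 months. With no statement of which analysis decides, the conclusion on a primary outcome could be chosen after the results are known.

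**Working it through.** **Inputs from the article.** 400 per arm; surveys at baseline and 3, 6, 9 and 12 months; two-sided 0.05. **Assumed**, because the article gives no rate per visit: the follow-up percentages below, and linear time coded 0 to 4.

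**The plan's own figure.** Power is stated only for standardized mean differences. For d = 0.22, n per arm = 2(1.96 + 0.84)²/0.22² ≈ 325, which is 81% of 400. The article gives no attrition rate, so this neither confirms nor contradicts the stated power. There is no power figure for treatment initiation to reproduce. The 325 serves below as a plausible number analysed per arm.

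**Step 1: linear-logit fit with baseline included.** The model is logit p = b0 + b1·t + b2·arm + b3·arm·t, fitted to expected proportions with 400 per arm and independent waves. Baseline is 0% in both arms; follow-up is 20% (BRAVE) and 10% (control) throughout.

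- Slope effect b3 = 0.03 (SE 0.08).
- Intercept effect b2 = 0.73 (SE 0.21).
- Fitted baselines are 8.8% and 4.4%; the true values are both 0%.
- Fitted 3-month log odds ratio = 0.73 + 0.03 = 0.76 (SE 0.15). The true value is ln[(0.20/0.80)/(0.10/0.90)] = ln 2.25 = 0.81.
- The joint 2-df likelihood ratio for intercept and slope is 63.

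The effect is present in the fit, but it sits in the intercept, and the slope alone shows nothing.

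**Step 2: simulated logistic latent growth models.** Baseline is 0%, follow-up is a constant 25% against 15%, with 325 per arm and latent correlation 0.6. Under these rates about 49% of BRAVE participants initiate at some time in 12 months, close to the article's 50%, against 33% of controls. Entries are the share of runs with a significant result favouring BRAVE.

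| Model | Slope effect | Baseline-intercept effect | Direct 3-month comparison |
|---|---|---|---|
| Random intercept (400 runs) | 6% | 77% | 90% |
| Random intercept and slope (150 runs) | 47% | 63% | 94% |

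The direct comparison does not depend on the growth model; its two entries differ only by simulation error. With 3% of participants reporting care at baseline, slope power is 19% and 53%, so an exact zero is not needed. A model fitted to the four follow-ups only, with its intercept at 3 months, detects the effect on the intercept in 94–98% of runs.

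**Step 3: a fading effect.** Repeat Step 1 with BRAVE at 20, 18, 16 and 15% and control at 10, 12, 14 and 15%.

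- With baseline: slope −0.17 (SE 0.07) and fitted 3-month log odds ratio 0.60 (SE 0.15). Adding −0.17 per visit gives 0.60, 0.43, 0.26 and 0.09, so the fit favours BRAVE at all four follow-ups.
- Without baseline: slope −0.27 (SE 0.09).

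The negative slope comes from the assumed convergence of the arms and becomes steeper when baseline is removed.

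**The case against.** The strongest reply is that the plan already contains a sound analysis: a logistic regression at each time point, including the stated primary one. That is right. A reader might infer that the trial cannot test whether BRAVE increases initiation; the text does not support this, because those regressions do not use baseline initiation. What remains is that the article adds them alongside the growth model without saying which decides.

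Use of the baseline wave is also an inference. The Primary Outcomes section describes this outcome as post baseline, and the Overview does not fix linear time or a time origin for it. A growth model of the follow-ups alone would be compatible with that section. But the Overview speaks of change in treatment initiation and sets the primary time point as baseline to 3 months, so the two sections at least need reconciling.

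The effect is not lost if intercept and slope are read together. A joint 2-df test keeps 98% power for the constant effect in the Step 2 setting, and 78% for a fading one. The plan regresses each factor on arm and names no joint test.

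Other stronger readings also fail:

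- A reader might infer that the zero baseline reverses a real benefit. Step 3 shows otherwise: a negative slope correctly describes a fading effect, and it remains without baseline.
- A reader might infer that baseline is exactly zero. The criterion concerns appointments, whereas the item also counts support groups and medications, so a few positive answers are possible.
- A reader might infer that the model cannot be fitted. Under linear time it gives finite estimates; they are just hard to interpret.
- A reader might infer that the 50% expectation cannot be examined. It is a one-arm figure in the power section, and four consecutive 3-month look-backs cover the year.

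The continuous label is a drafting slip, since the same paragraph also calls the outcome binary and assigns it categorical methods. An SAP might settle the ranking of analyses and the coding of time, but the article itself states a growth model of change for an outcome whose baseline its own criteria set at or near zero.

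**Conclusion.** The point holds in a limited form. On the natural reading of the Overview, a stated analysis of a primary outcome has an intercept and a slope that do not, read singly, measure whether BRAVE increases initiation. In the illustration, a doubling from 10% to 20% at every visit gives a slope of 0.03 (SE 0.08) and a false fitted baseline gap of 4.4 percentage points (8.8% − 4.4%). In simulated growth models with 25% against 15%, slope power is 6% or 47% depending on the random-effects structure, against 90–94% for the direct 3-month comparison.

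These sizes rest on assumed visit rates, linear time, a baseline at or near zero and, in the simulation, an assumed correlation. The displacement of a constant effect into the intercept follows from the design; its size does not. The trial can still estimate the effect through the logistic regressions. What must be settled is which analysis decides and where the growth model begins.

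**What to change.** In the Overview of the Analytic Plan:

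1. Name the 3-month logistic regression on arm as the primary test of treatment initiation.
2. Fit any growth model for this outcome to the four follow-ups only, with the intercept at 3 months, so that the arm effect on the intercept is the 3-month effect. Present it as supportive.
3. Remove treatment initiation from the list of continuous outcomes.
4. As a secondary analysis, report any initiation over 12 months by arm, built from the four 3-month look-backs, to match the hypothesis in the Power Analysis section. State how a missed survey is handled.

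The cost is a few sentences. The growth model gives up one wave that carries almost no information on this outcome. No extra participants, visits or items are needed. Rewording the item to cover the time since the last completed survey would be optional.

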We will test for significant effect moderation by the following variables: barriers to care, PTSD, depression, and severity of AUD symptoms. To explore moderation, we will use simple linear regression models for primary outcomes at each time point. We will include an interaction term between each potential moderator and the intervention indicator (BRAVE vs control). Significant interactions between the intervention group and these moderators will be plotted with appropriate values and interpreted. Simple slopes will be calculated for all significant interactions. Given our prior work and the large sample size, we expect to have adequate numbers of participants in each cell for moderation analyses and will use established cutoff scores on the PCL-5 (score 33 or higher vs under 33), PHQ-8 (scores 10 or higher vs under 10), and the AUDIT (scores 8 or higher vs under 8). We hypothesize that those with greater barriers, PTSD, depression, and severity of AUD symptoms will benefit most from the intervention. Sex (male or female) will be included as an exploratory moderator.

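### The moderation regressions and the additional per-wave logistic models use only the wave being analysed, so direct maximum likelihood reduces there to available cases

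*Protocol article*

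**What the plan says.** All of this stands in the Protocol article, Analytic Plan, Overview, unless noted.

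- **Missing data.** One rule is given before any model is named: "Missing data will be assumed to be missing at random and handled using direct maximum likelihood techniques".
- **Treatment initiation.** This is one of the primary outcomes. The plan is to fit a growth model for categorical outcomes and, in addition, to "estimate simple logistic regression at each time point". The growth model comes first and the per-wave logistic model is additional. The text does not say which of the two is primary.
- **Moderation (Aim 2).** "To explore moderation, we will use simple linear regression models for primary outcomes at each time point", with a moderator-by-arm product term. PCL-5, PHQ-8 and AUDIT are split at established cut-offs. No longitudinal model is named for this aim.
- **Covariates.** The only adjustment rule adds demographic or military characteristics that turn out to differ significantly between the arms.
- **Power Analysis.** With "standard *P*<.05; 2-tailed testing" and 80% power, the detectable effects are d=0.22 at 3 and 6 months and d=0.23 at 9 and 12 months. No retention rate is given.

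**The concern.** Direct maximum likelihood uses an incomplete record through the other variables in the same model. A growth model contains the other waves, so a participant who misses one wave still contributes. A regression of one wave on arm, or on arm and moderator, contains no other outcome. If the outcome at that wave is missing, the record carries no information about the coefficients. The stated rule is then met in name only.

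Such a fit is valid if missingness depends only on what is in the model. It is not valid in general if missingness depends on baseline drinking, symptom severity or earlier outcomes that the model leaves out. The covariate rule does not help, because it selects on chance imbalance and not on prediction of dropout or outcome. It also does not reach baseline drinking or the severity scores.

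At stake are all the Aim 2 tests, for which no other model is named, and the time-specific odds ratios for treatment initiation. Leaving out the baseline outcome also costs precision, which matters most for interactions.

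**Working it through.** **1. How much missing data the plan appears to expect.** Inputs from the article: 400 per arm, two-sided 0.05, 80% power, d=0.22 and 0.23. The number needed per arm is n = 2 × ((1.960 + 0.842)/d)².

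| d | n per arm | share of 400 | implied missing | range from rounding of d |
|---|---|---|---|---|
| 0.22 | 324.3, so 325 | 81% | 19% | 15% to 22% |
| 0.23 | 296.7, so 297 | 74% | 26% | 22% to 29% |

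With all 400 per arm, the detectable effect would be 2.802 × √(2/400) = 0.198. Retention of 80% gives 2.802 × √(2/320) = 0.221, and 75% gives 2.802 × √(2/300) = 0.229. Both match the stated figures after rounding. The article does not state these rates, so the match is an inference.

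**2. Per-wave logistic model, no true effect.** All inputs here are assumptions. Baseline severity x is standard normal. The outcome logit is −1.0 + 0.8x in both arms, which gives about 29% events. The retention logit is 1.55 + g·x, and the odds ratio is unadjusted among observed participants.

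| g in BRAVE | g in control | retention, BRAVE / control | odds ratio (truth 1.00) |
|---|---|---|---|
| −0.6 | −0.2 | 81% / 82% | about 0.94 |
| −0.8 | +0.2 | 80% / 82% | 0.87 |
| −0.4 | −0.4 | 82% / 82% | 1.00 |
| −0.8 | −0.8 | 80% / 80% | 1.00 |

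Other slope pairs between the first two rows fall between 0.87 and 0.94. Retention differs by less than 3 points throughout, so comparing retention rates would not reveal the problem. With x added to the regression, the odds ratio was between 0.99 and 1.01 in every scenario.

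For scale, at 325 per arm and 29% events the standard error of the log odds ratio is √(2/(325 × 0.29 × 0.71)) = 0.17. The bias is ln 0.94 = −0.06 to ln 0.87 = −0.14.

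**3. A later wave, with missingness driven by an earlier outcome.** Assumptions: correlation 0.6 between waves and 26% missing.

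- With the same mechanism in both arms, a true log odds ratio of 0.41 is estimated as 0.42.
- With missingness slopes of 0.75 against 0.25, it falls from 0.40 to 0.29.
- With slopes of 1.0 against 0.0, a deliberately extreme case, it falls from 0.41 to 0.18.
- For a continuous outcome with a true contrast of −0.22, the available-case estimates are −0.218, −0.288 and −0.352. An estimate that uses the earlier wave stays at about −0.22.

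**4. Moderation model.** The dropout mechanism is that of step 2. The outcome is continuous with SD 1, correlates 0.5 with baseline severity, and has no true effect.

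- Severity entered as a continuous moderator: interaction bias 0.00.
- Severity split at its median: interaction bias about 0.02 to 0.03 SD.
- Split moderator, with the continuous baseline value added: bias back to about zero.

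For scale, four cells of about 162 participants give an interaction standard error near √(4/162) = 0.16 SD.

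**5. Precision.** Adjusting for a baseline value that correlates ρ with the outcome removes about ρ² of the residual variance. At an assumed ρ of 0.6 that is 36%, and about a third among observed participants in the simulation. At ρ=0.5 it is 25%. In a moderation model the gain is smaller to the extent that the moderator already explains the outcome.

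**The case against.** The strongest reply has four parts.

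- **The growth model.** Treatment initiation is also analysed with a categorical growth model, which falls under the maximum likelihood rule. This stands. A reader might infer that the outcome rests on complete-case logistic regression alone; the text does not support that. The concern there covers only the additional per-wave odds ratios.
- **Dropping is not stated.** A reader might infer that the plan contradicts its own rule and discards participants. No sentence says so, and the rule is not limited to the growth models. What remains follows from the named models: applied to a single-wave regression, the rule has nothing to work with. A condensed article may leave auxiliary variables and imputation to a fuller document, so their absence is not the point. The point is the choice of a simple regression.
- **The mechanism is chosen.** Bias appears only when dropout depends on severity differently by arm. Nothing in the article shows that it will, and surveys and payments are the same in both arms. This also stands, and it limits the claim to a possibility. Differing dropout is plausible, since only BRAVE participants receive feedback on their own drinking, but that is a judgement.
- **The growth models are not fully protected either.** Eligibility excludes behavioral health appointments in the past six months, so baseline initiation is nearly constant. No follow-up wave precedes 3 months. A participant lost straight after baseline therefore adds almost nothing to the initiation growth model. This is correct, and it is why the fix relies on baseline severity and drinking for that outcome.

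**Conclusion.** The concern holds in a limited form. As named, the moderation regressions and the additional per-wave logistic models are available-case analyses, although the plan's general rule suggests more. With roughly 20% to 25% of outcomes apparently expected to be missing, the choice is not trivial.

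The likely harm is modest. There is essentially no bias under a common dropout mechanism. Under the arm-specific slopes of step 2, the odds ratio is 0.87 to 0.94 in place of 1.00, which is less than one standard error. The interaction bias of 0.02 to 0.03 SD is about a fifth of its standard error or less. Larger distortion needs the steeper mechanisms of step 3. The loss of precision is the more certain cost, because it does not depend on any dropout mechanism.

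These sizes rest on assumed correlations, event rates and dropout slopes, none of which the article gives. A reader might go further and infer that the Aim 2 results will be seriously biased; neither the article nor the calculations support that.

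**What to change.** 1. In every per-wave model for drinking or consequences, including the moderation models, adjust for the baseline value of the outcome, whether or not the arms differ on it.
2. In the treatment-initiation models, adjust for baseline AUDIT, PCL-5, PHQ-8 and drinking, because baseline initiation is nearly constant by eligibility.
3. Choose one of two routes for missing outcomes. Either test moderation and take the time-specific odds ratios from the longitudinal model with these covariates, or run the per-wave models on multiply imputed data whose imputation model contains these covariates and the other waves.
4. State which treatment-initiation model is primary.

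The cost is a little more analysis work. All the variables are already collected, and neither the design nor the sample size changes. It is a cheap improvement.

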#### Moderators

To examine the characteristics of participants for whom the intervention is most efficacious, we will include measures at baseline of perceived barriers to treatment, PTSD symptoms, depression symptoms, and AUD severity. Perceived barriers are assessed with the 15-item RAND Barriers to Mental Health Care item bank [70]. Items are rated on a scale from 1 (not at all) to 5 (very much) and reflect barriers of perceived stigma (eg, seeking care would be viewed as a sign of personal failure, others would lose respect for the person, and other veterans would see them as weak), fears about confidentiality (eg, people might find out about it), beliefs that treatment does not work, and difficulties finding time for treatment due to other responsibilities (eg, because of work or family). These items can be summed to receive a baseline severity of barriers score. PTSD symptoms will be assessed with the 20-item PTSD Checklist (PCL-5), a widely used measure for military and veteran populations with adequate reliability and validity for young adult military samples [71]. Depression symptoms will be assessed with the Patient Health Questionnaire 8-item (PHQ-8), a reliable and valid measure of depression used in research and practice for military and veterans [72-74]. The severity of AUD will be assessed with the AUDIT [54], a 10-item alcohol screen that identifies individuals who had probable AUD in the past year. The PCL-5, PHQ-8, and AUDIT can each be summed to create baseline symptom severity scores for each.

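### Moderation is tested by linear regression on every primary outcome, including a binary one, and with dichotomised symptom scales, so subgroup claims can depend on an unstated scale and lose information

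*Protocol article*

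**What the plan says.** **Moderation model.** In the protocol article, Methods, Analytic Plan, Overview, the moderation paragraph reads: "To explore moderation, we will use simple linear regression models for primary outcomes at each time point". It adds: "We will include an interaction term between each potential moderator and the intervention indicator (BRAVE vs control".

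**Outcomes covered.** Under Measures, Primary Outcomes: "Primary outcomes are drinking behavior (past 30-day frequency, quantity, and number of binge-drinking days), negative alcohol-related consequences, and treatment initiation". The drinking items are two day counts and a quantity: "Three past 30-day drinking outcomes will be assessed through single-item self-reports: drinking days, average drinks per occasion, and binge drinking days".

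**Main-effect models.** Earlier in the same Overview: "For any count variables, negative binomial or Poisson distributions will be explored for better model fit". Treatment initiation is first listed among the continuous outcomes. It is then called binary and assigned categorical latent growth models, plus logistic regression at each time point. The moderation paragraph does not carry these models over.

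**Moderator coding.** The plan "will use established cutoff scores on the PCL-5 (score 33 or higher vs under 33", and likewise splits PHQ-8 at 10 and AUDIT at 8. Barriers to care has no cutoff, and sex is binary by nature. Under Measures, Moderators: "The PCL-5, PHQ-8, and AUDIT can each be summed to create baseline symptom severity scores for each".

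**Hypothesis.** Specific Aims and Hypotheses and the moderation paragraph both predict that participants with more barriers or more severe symptoms gain most. The Discussion says that subgroup results could support targeting dissemination.

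**The concern.** Whether an interaction exists depends on the scale. If BRAVE lowers binge days by the same proportion in everyone, the absolute fall is larger where drinking is heavier. A linear interaction then departs from zero although the rate ratio is constant. AUDIT severity is closely tied to drinking level, so the departure lies in the direction that Aim 2 predicts. The same can happen for initiation if baseline-severe participants start treatment more often anyway.

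A reader of the results could then meet a main effect reported as an odds ratio or rate ratio beside a subgroup finding from a linear model, with nothing to say that the two are on different scales. A decision to target dissemination could rest on that finding.

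Dichotomising is a separate matter. It does not cause the scale problem, but it weakens tests that already have little power.

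**Working it through.** **1. The plan's own figure.** Power Analysis gives a detectable d of 0.22 (3 and 6 months) and 0.23 (9 and 12 months) at 80% power, two-sided 0.05. With d = 2.80 × √(2/n):
- all 400 per arm gives d = 0.198;
- d = 0.22 needs 325 per arm (81% of 400);
- d = 0.23 needs 297 per arm (74% of 400).

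The figures match if about 80% and 75% are retained, but the article states no retention. It gives no figure for the moderation tests. Below, 640 analysed (80% of 800) is an assumption.

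**2. Size of interaction the design can detect.** With a binary moderator and SD 1, the standard error is √(sum of 1/n over the four cells).
- 50/50 split: √(4/160) = 0.158, times 2.80 = 0.44.
- 30/70 split: √(2/96 + 2/224) = 0.173, times 2.80 = 0.48.

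That is about twice the main-effect d.

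**3. Counts, constant rate ratio 0.8.** The article gives no means, dispersion or stratum shares. Assumed: control means 3 vs 6, 3 vs 9 or 2 vs 8; negative binomial variance μ + kμ² with k = 0.6 to 1.0; 50% or 70% in the high stratum.

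One setting by hand (2 vs 8, k = 1, 50/50, 160 per cell):
- absolute reductions are 0.4 and 1.6 days, so the linear interaction is −1.2;
- cell variances are 6, 72, 4.16 and 47.36, sum 129.52;
- SE = √(129.52/160) = 0.90, z = 1.2/0.90 = 1.33;
- rejection probability is about 27%, and simulation gave 26.7%.

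Simulation over all settings (4,000 runs each, ordinary standard errors):

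| Common rate ratio | Overall d | Linear interaction rejected |
|---|---|---|
| 1.0 (no effect) | 0 | about 5% (50/50); 0.5-1.4% (70% high) |
| 0.8 | 0.14-0.22 | 5-37% |
| 0.7 | 0.24-0.36 | 12-74% |

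At 0.8, nearly all rejections say that heavier drinkers benefit more. In four of those settings both models were fitted: the linear model rejected in 5-30% and negative binomial regression in 4.1-5.7%. Robust standard errors are no cure. At 2 vs 8, k = 0.6 and 70% high, they raised rejection from 17% to 44%, because they detect better an interaction that does exist on the absolute scale.

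**4. Initiation, constant odds ratio 2.** Treated risk = 2o/(1 + 2o), with o the control odds. Control risks are assumed, with a 50/50 split.

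| Control risks, low vs high stratum | Risk differences (points) | Linear interaction rejected |
|---|---|---|
| 10% vs 30% | 8.2 vs 16.2 | 23% |
| 5% vs 15% | 4.5 vs 11.1 | 23% |
| 10% vs 20% | 8.2 vs 13.3 | 13% |
| 15% vs 25% | 11.1 vs 15.0 | 9% |
| 25% vs 50% | 15.0 vs 16.7 | 5.6% |

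Logistic regression, run for 10/30, 5/15 and 10/20, rejected in 4.8-5.4%.

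**5. Information kept after a cut.** For a normal score with a linear gradient, the share kept is φ(c)²/[p(1−p)], where p is the share above the cut c.
- p = 0.5: 0.637, or 407 effective of 640.
- p = 0.3: 0.576, or 368.
- p = 0.2: 0.490, or 314.

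**The case against.** The strongest reply has four parts.

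- **Count models are only to be explored.** The drinking outcomes may stay in linear growth models and be reported as Cohen d. Arm effect and moderation would then share a scale. This stands: the mismatch is firm only for initiation and conditional for the counts.
- **A larger absolute reduction is a real difference.** Aim 2 asks who gains most in terms of drinking reductions, which can be read on the absolute scale. This also stands. The fault is not naming the scale.
- **The cutoffs are established and suit subgroup questions.** Having summed scores does not contradict cutting them, since a score must be summed before it is cut. That is fair, but it is a reason to display results at the cutoffs, not to test there. The retained-information figures are approximate. AUDIT in particular is truncated by the entry criteria (4 or more for men, 3 or more for women), so normality is doubtful.
- **An analysis plan not shown may refine this.** It may, but linear regression and the cutoffs are stated choices, not silences.

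A reader might also infer that the moderation models leave out the baseline outcome and use complete cases only. The article does not say so. It gives no covariate list for these models, and its missing-data statement, "Missing data will be assumed to be missing at random and handled using direct maximum likelihood techniques", stands in the general Overview and is not limited to Aim 1.

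**Conclusion.** The point holds in limited form. The plan names linear regression for a binary primary outcome that it elsewhere analyses by logistic and categorical models, and for counts that it may analyse on a log scale. A non-zero effect that is proportional across strata can then register as moderation in the hypothesised direction: about 5-37% of trials at a rate ratio of 0.8, and about 6-23% at an odds ratio of 2. These ranges rest on assumed means, dispersion, control risks, stratum shares and 80% retention. The mechanism is argued mainly for AUDIT on the drinking outcomes. The article gives nothing on how drinking differs by PTSD, depression or barriers.

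A reader might infer that the linear model manufactures false interactions, or that Aim 2 would be confirmed by the choice of scale. That is not supported. Without an effect there is no inflation, some settings stay near 5%, and even 37% is far from certain confirmation.

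The loss from cutting three of the four hypothesised moderators is about 36% to 51% of the information for splits from 50/50 to 20/80, under normality and a linear gradient. The change is worth making, but it does not touch the primary comparison.

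**What to change.** Reword the moderation paragraph as follows.

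- Test each interaction in the model family used for that outcome's main effect: logistic or categorical for initiation, and negative binomial or Poisson for counts where adopted. If a drinking outcome stays linear, its interaction may too.
- Enter PCL-5, PHQ-8, AUDIT and barriers as continuous scores multiplied by arm. Use the cutoffs only as values at which simple slopes are shown.
- State the scale on which moderation is claimed, and report absolute subgroup differences descriptively.

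This costs wording only and needs no new data. The small downside is that a linear gradient on the link scale is assumed; a spline can check it.
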